## Abstract

**Background:**

Previous research revealed several biological and environmental factors modulating cognitive functioning over a human’s lifespan. However, the relationships and interactions between biological factors (eg, genetic polymorphisms, immunological parameters, metabolic products, or infectious diseases) and environmental factors (eg, lifestyle, physical activity, nutrition, and work type or stress at work) as well as their impact on cognitive functions across the lifespan are still poorly understood with respect to their complexity.

**Objective:**

The goal of the Dortmund Vital Study is to validate previous hypotheses as well as generate and validate new hypotheses about the relationships among aging, working conditions, genetic makeup, stress, metabolic functions, the cardiovascular system, the immune system, and mental performance over the human lifespan with a focus on healthy working adults. The Dortmund Vital Study is a multidisciplinary study involving the Departments of Ergonomics, Immunology, Psychology and Neurosciences, and Toxicology at the Leibniz Research Centre for Working Environment and Human Factors at the Technical University of Dortmund (IfADo) in Germany, as well as several national and international partners.

**Methods:**

The Dortmund Vital Study is designed as a combined cross-sectional and longitudinal study. Approximately 600 healthy subjects aged between 20 and 70 years will participate. A wide range of demographic, psychological, behavioral, sensory, cardiovascular, immunological, and biochemical data, a comprehensive electroencephalography (EEG)-based cognitive test battery as well as structural and functional magnetic resonance imaging (MRI) have been included in the study.

**Results:**

The study was approved by the Ethics Committee of IfADo in October 2015. The baseline testing was conducted between 2016 and 2021 and will be repeated every 5 years (3 follow-up measures until 2035). As of March 2020 (until the outbreak of the COVID-19 pandemic), 593 participants have been enrolled. Some results from the cross-sectional part of the study were already published, further results will be published soon. Longitudinal data will be analyzed and published by 2025.

**Conclusions:**

We anticipate that the study will shed light on sources of interindividual differences in the alterations of cognitive functioning with increasing age and reveal biological and lifestyle markers contributing to work ability, longevity, and healthy aging on the one hand, and to risk factors for cognitive decline, mild cognitive impairment, or even dementia on the other hand.

**Trial Registration:**

ClinicalTrials.gov NCT05155397; https://clinicaltrials.gov/ct2/show/NCT05155397

**International Registered Report Identifier (IRRID):**

DERR1-10.2196/32352

## Introduction

### Background

Cognitive performance in humans is a complex phenomenon that is influenced by numerous variables. Among them are age [1,2], various infections [3,4], inflammatory processes often due to the release of cytokines from immune cells [5,6], metabolic alterations such as hyperammonemia [7,8], lifestyle factors including physical and mental activity, type of work, nutrition and stress [9-16], as well as numerous genetic variants [17,18] that can be analyzed by polygenic scores [19]. Most studies in this field of research have focused on specific individual factors of influence and did not consider the development of individuals over a significant part of their lifetime. To bridge this gap, we initiated the Dortmund Vital Study that assesses cognitive performance in a longitudinal study design using a complex multiscale approach to understand the influence of the most important lifestyle, occupational, and biological factors on cognitive performance.

### Research Questions and Aims

The aim of the Dortmund Vital Study is to evaluate the effect of several endogenous and exogenous parameters and their complex interaction on behavior and the underlying neuronal activity. This will be achieved by implementing cross-sectional and longitudinal designs. By repeated measurements of the endogenous and exogenous parameters over an extended period, risk factors for possible cognitive impairment associated with depression, occupational burnout, or age-related diseases, such as mild cognitive impairment or dementia, and nonpathological cognitive decline shall be identified. More importantly, the Dortmund Vital Study focuses on the following research aspects, which are currently poorly understood and largely unexplored:

Liver Immune Behavior-Brain Axis: A core question is how specific aspects of cognitive performance and brain activities as well as the brain structure are affected by metabolic products, inflammatory mediators, or viral infections, including concentrations of metabolites such as creatinine, ammonia, or immunological parameters in the blood such as inflammatory cytokines, and novel metrics of immunological age. Combinations of standardized cognitive tests and electroencephalographic techniques with computer-based tests, as well as structural and functional magnetic resonance imaging (MRI) will be used to explore cognitive performance with a much greater level of detail compared to previous studies.Multidimensional and Multichannel (Omics) Analyses: The roles of metabolic parameters or inflammation mediators have traditionally been determined by analyzing individual effects of the selected parameters per study. However, with currently available techniques and technologies, it is possible to measure a wide range of parameters (ie, metabolites, proteins, RNA species, DNA variants, and immune cells) simultaneously, using the so-called “omics” techniques or multichannel analysis. Consequently, a more comprehensive picture is obtained, which can then be evaluated using systems biology techniques to understand the interactions among the individual factors.Age-Related Perspective: Temporal dynamics of the interplay between endogenous versus exogenous factors and cognitive functions, as well as work ability over the lifespan will be assessed. In particular, the effect of metabolic products, infections or inflammatory processes, and the brain structure and function on neurobehavioral parameters in young, middle, and old age will be analyzed in a cross-sectional design.Disease-Related Perspective: With the present design, the derivation and evaluation of risk factors for widespread mental and neurodegenerative diseases such as depression, burnout, mild cognitive impairment, or dementia will be addressed. Moreover, epigenetic approaches that investigate the influence of environmental changes on the genome, as well as on the brain structure and function will be feasible. Epigenetic dysregulation is also important for the development of immunological and neuronal diseases and complex developmental disorders.Genetic Perspective: Although it is known that genes influence cognitive performance, which in turn is associated with the structural and functional network efficiency of the brain, functional understanding of the specific brain parameters that mediate the relationship between individual genetic variations or polygenic scores and cognitive performance is incomplete. Given that the current study will capture all relevant neurocognitive measures, it will be possible to investigate the interactions among genes, brain parameters, and cognitive performance.Longitudinal Perspective: Most existing studies have only used cross-sectional study designs that limit the interpretation of results, given that the results obtained in cross-sectional studies do not imply causality. Therefore, this study has been additionally designed as a longitudinal study with postmeasures every 5 years. The advantage of such a longitudinal study is that parameters, namely particular metabolic or immunological states, genetic variations, or brain metrics, can be recorded at an early stage and then be tracked to test whether they result in any effect later; moreover, one can investigate how the state of these parameters changes over the course of a person's life. This design allows causal inferences.

The benefit of the Dortmund Vital Study will be that profound knowledge regarding the interactions among metabolism, the immune system, genetics, the brain structure and function, and cognition will be gained. In the long run, this knowledge will lead to empirically based intervention strategies to preserve cognitive functioning, work ability, and promote healthy cognitive aging. The strength of the study design lies in the fact that variables with an impact on cognitive performance and their interactions can be determined comprehensively and that factors whose significance is still unknown today will be identified and evaluated. Due to the complex design and several measurement parameters, a wide range of research questions is possible. Given below are 4 of several hypotheses possible in the study.

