## Methods

### Study Population

The participants of the Dortmund Vital Study (trial registration number: NCT05155397) represent a sample of a generally healthy population of a western society aged between 20 and 70 years. We define “healthy” in a rather broad sense and allow the inclusion of individuals who are smokers, drink alcohol, are overweight, or have a history of diseases without having severe symptoms. Moreover, we do not impose restrictions regarding education or occupation to enhance the representativity of the sample. Participants are recruited via an internet site, newspaper advertisements, reports and announcements in local print and radio media, public information events, social media, and flyers throughout the city of Dortmund, Germany. In addition, some larger companies in the region were contacted and asked to inform their employees about participating in the study. The number of subjects resulted from a biostatistical estimation (power analysis), in which the size of the expected effects and their variance were considered. The study parameters will be collected repeatedly for 4 time points, namely at the start of the study (baseline), and then 5, 10, and 15 years later (time points for measuring within-subject factors) and between 3 age groups (between-subject factor ie, Age Group: young, middle-aged, and old). Of particular interest here is the interaction between the age group and the measurement time point, which will provide insight into the different trajectories within the specific age groups. Thus, power estimation was conducted exemplarily for repeated-measures analyses of variance (ANOVA) of within-between interactions. The sample size was determined based on a small effect size of *f*=0.1 for the mixed ANOVA model with repeated measures (4 time points) and interactions with the Age Group factor (3 categories), given an error probability of α=.05 and a power of 0.95, resulting in a sample size of 264 individuals (determined with G*Power, a free-source statistical software package) [44]. However, having a larger number of subjects is desirable owing to expected dropouts over the long duration of the study. Therefore, a group size of approximately 600 was targeted, as we assumed a dropout rate of up to 20% per time point of the follow-up measures. Assuming this dropout rate, the number of remaining participants 20 years later would be approximately 300, which roughly corresponds to the estimated sample size, as summarized in Table 1.

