### Data Analysis

Detailed descriptions of the specific data analysis methods depending on the type of measure will be provided in subsequent publications.

Generally, for all quantitative variables, descriptive statistics, frequencies, and distributions will be calculated for all participants. Summary statistics including the mean, SD, minimum values, and maximum values will be provided for quality assurance. Qualitative variables will be categorized before performing any statistical analysis. Immunological, biochemical, medical, optometric, and audiometric data as well as coding for genetic polymorphisms are integrated in the SQL database. Data from psychometric tests in the SQL database will be verified by using an automated MATLAB script for plausibility and outliers. EEG and behavioral data from experimental tasks will be analyzed with EEGLAB [108] using scripts. The main parameters, such as individual amplitudes or latencies of transient components, time-frequency parameters, or behavioral data, such as reaction times, error rates, and SDs, will be automatically written in the SQL database.

Depending on the research topics and questions, different methods will be used for data analysis. For the cross-sectional analyses, mixed ANOVA, Analyses of Covariance (ANCOVA), 1-way ANOVA, or *t* tests will be used. Furthermore, the Pearson correlation coefficient or appropriate regression models will be used to identify predictors of the variables of interest. Moreover, the structural equation modeling approach and novel decoding techniques will be employed when appropriate.

For the longitudinal data, mixed model ANOVA including within-subject factors, such as Time Point of Measure, and between-subject factors, such as Age Group, will be employed. Interactions will be analyzed using simple ANOVA or *t* tests. Additionally, covariance analysis (ANCOVA) will be conducted to control for potential confounding factors like gender and education. It is not intended to impute missing data for ANOVA or ANCOVA. In case of a few or moderate number of missing data, the analyses will be conducted with the complete cases. In case of a larger number of missing data over the long period, advanced statistical approaches like the Generalized Estimating Equation (GEE) [109] or Mixed Effect Regression (MER) [110] will be used.

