For the present design, a GEE [109] model will be used, which is robust to misspecifications of the repeated measures’ correlation structure, time irregularities, and does not require excluding participants with incomplete data sets. An alternative method would be MER [110], in which random effects can serve to describe each participant’s trend over time. MER assesses longitudinal changes of several outcomes and is even more robust to missing data than the GEE. Both models allow time-invariant predictors (eg, biological gender, genotype) and time-varying predictors (eg, age, metabolic, immunological, or cognitive parameters), and handle irregularly timed and missing data without the need for imputation [118]. An advantage of these procedures is that both can model time-varying predictions useful for understanding changes in cognitive aging.

Nevertheless, the relatively large number of participants in this study that primarily aims to analyze cognitive changes using neuropsychology, EEG, and MRI is unique and even taking dropouts into account allows answering important scientific questions. For example, when interested in age-related changes in an electrophysiological parameter, a group of approximately 40 participants would still be sufficient to track the changes across the span of 20 years. Generally, we expect the dropout rate to remain constant and to be able to analyze the data with a sufficiently large sample at least for the first follow-up measures 5 and 10 years after the beginning of the study.

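### The article credits the longitudinal design itself with allowing causal inferences; in a volunteer cohort, repeated measurement gives temporal order only, and no identifying assumptions are stated

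*Protocol article*

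**What the plan says.** The Longitudinal Perspective item in Research Questions and Aims argues that most existing studies are limited because they are cross-sectional, "given that the results obtained in cross-sectional studies do not imply causality". It says this study was for that reason also made longitudinal, with measurements every 5 years, and it closes with "This design allows causal inferences".

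Other sections describe the setting in which that sentence must hold:

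- **Design** (abstract, Methods): "The Dortmund Vital Study is designed as a combined cross-sectional and longitudinal study". No exposure is randomised or assigned.
- **Recruitment** (Study Population): "Participants are recruited via an internet site, newspaper advertisements, reports and announcements in local print and radio media", along with other public channels and some larger employers.
- **Confounding** (Data Analysis): "covariance analysis (ANCOVA) will be conducted to control for potential confounding factors like gender and education".
- **Longitudinal model** (Data Analysis): "For the longitudinal data, mixed model ANOVA including within-subject factors, such as Time Point of Measure", with Age Group between subjects. GEE or mixed-effects regression (MER) is kept for the case of many missing data. Limitations and Future Challenges reads differently: there a GEE is to be used, with MER as the alternative.
- **Predictors** (Limitations and Future Challenges): both models are said to accommodate time-invariant predictors such as genotype and "time-varying predictors (eg, age, metabolic, immunological, or cognitive parameters").

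Data Analysis leaves the detailed description of methods to later publications.

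**The concern.** Recording a state early and a cognitive outcome later settles which came first. It does not settle whether the first produced the second. A stable characteristic can drive both, early cognitive change can alter later stress, activity or metabolic state, and those who return at later waves may differ from those who do not. The article presents the step from cross-sectional to longitudinal as sufficient for causal inference and names nothing else that would carry it.

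The sentence has consequences. The Study Overview in the Discussion announces conclusions about which past factors weigh most on present measures or on outcomes such as burnout and dementia. Hypothesis 3 proposes to find out whether long-term stress cancels the benefit of education, or whether exercise makes up for having less of it. The Introduction expects the knowledge gained to lead to intervention strategies. All of these are causal uses. If they rest on temporal order alone, stable differences between people or reverse causation could be reported as effects.

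**Working it through.** **1. What a causal reading needs, against what the article supplies**

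- *Control of confounding.* No exposure is assigned. Gender and education are named as examples of ANCOVA covariates. The Questionnaires section shows that many other candidates are measured (smoking, employment history, childhood trauma, chronic stress). No assumption is stated under which any adjustment set would suffice.
- *No reverse causation, or a method that handles it.* Cognition is the main outcome, yet cognitive parameters also appear among the time-varying predictors. Hypothesis 3 expects psychosocial stress to influence immune or metabolic parameters, so a later covariate may lie downstream of an earlier exposure. No method for this is named.
- *Dropout unrelated to the outcome, or modelled.* Limitations and Future Challenges expects illness and death to remove older participants disproportionately. Table 1 allows 20% loss per follow-up: 600 × 0.8 = 480, × 0.8 = 384, × 0.8 = 307. By the fourth wave 600 − 307 = 293 people, 49%, may be gone. The section treats this as a missing-data and power problem and does not link it to causal interpretation. It does not discuss confounding or reverse causation.

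**2. Figures in the article**

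The causal sentence rests on no figure. The sample size of 264 is for the Age Group by time interaction (f = 0.1, 3 groups, 4 waves, α = .05, power 0.95). With a correlation among waves of 0.5 and sphericity assumed, since neither is stated, the noncentral F calculation gives 263, or 264 in equal groups. It reproduces and is unaffected by this point.

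**3. Size of the blending risk if a time-varying predictor is entered undivided**

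The article gives no inputs for this, so all are assumed. Take m = 4 waves, predictor variance 1 with ICC p, and residual ICC of the outcome r.

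- Between-person sum of squares per person: B = m(p + (1 − p)/m). Within-person: W = (m − 1)(1 − p).
- Weight on the between-person slope, independence GEE: B/(B + W).
- Weight, random-intercept model or exchangeable GEE: b/(b + w), with b = B/(1 + (m − 1)r) and w = W/(1 − r).

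With p = r = 0.6: B = 4 × 0.7 = 2.8 and W = 3 × 0.4 = 1.2. The independence weight is 2.8/4.0 = 0.70. For the random-intercept model b = 2.8/2.8 = 1.0 and w = 1.2/0.4 = 3.0, so the weight is 0.25.

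Let the within-person effect be 0 and the between-person slope 0.30. The answer depends on what that slope refers to:

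- Slope on the observed four-wave mean: 0.70 × 0.30 = 0.21 (independence GEE) and 0.25 × 0.30 = 0.075 (MER).
- Slope on the true person level: the slope on the observed mean shrinks to 0.30 × 0.6/0.7 = 0.257, which gives 0.18 and 0.064.

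A simulation over a range of ICCs (600 people, 4 waves, 60 runs per setting, within-person effect 0, slope 0.3 on the true person level, residual ICC 0.5) gave:

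| Predictor ICC | MER and exchangeable GEE | Independence GEE | MER runs with p < 0.05 | Within-person term after splitting |
|---|---|---|---|---|
| 0.3 | 0.033 | 0.094 | 38% | 0.005 |
| 0.5 | 0.060 | 0.150 | 87% | 0.002 |
| 0.7 | 0.112 | 0.213 | 100% | 0.005 |

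With 60 runs the percentages are rough; the standard error of the 38% is √(0.38 × 0.62/60) ≈ 6 points. The pattern is clear: the undivided coefficient is non-zero although nothing changes within people, and separating the person mean from the deviation brings the within-person term back to about zero.

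**The case against.** The strongest defence is that the sentence says the design allows causal inference, by contrast with cross-sectional work, and that observational cohorts can support causal estimates under stated assumptions with suitable methods. That is right. A reader might infer that such a cohort can never deliver causal conclusions, and the documents do not support going so far. What remains is that the article credits the design alone and gives no assumption or method.

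Four further readings are tempting and should be resisted.

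- *That the planned coefficients do mix between- and within-person effects.* The article does not fix how predictors enter the model and defers such detail. The mixing is a foreseeable risk, not a stated error, and it does not arise for genotype or other time-invariant predictors.
- *That GEE or MER is the settled analysis.* Data Analysis puts mixed ANOVA first. The Age Group by time interaction used for the sample size does not involve the between/within question. Mixed ANOVA or ANCOVA would not remove unmeasured confounding either, so the main point is unaffected.
- *That adjustment is limited to two covariates.* The wording is "to control for potential confounding factors like gender and education", so these are examples.
- *That 0.21 or 0.075 is the expected bias.* Both rest on assumed ICCs and slopes, and 0.21 also needs an independence working correlation that the article never specifies.

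It can also be said that this is one Introduction sentence in a study with many hypotheses. That limits the cost of the correction. It does not limit the reach of the sentence, because the announced conclusions depend on it.

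**Conclusion.** The point holds as a misstatement of what the design provides. Temporal order is established. Freedom from confounding, reverse causation and selective dropout is not, and the article itself expects the last of these in older participants. No identifying assumption or causal method is given, and the limitations do not fill the gap. The sentence should be corrected because it governs how the study's conclusions will be read.

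No sample size, attrition figure or stated analysis in the article changes. The blending of between- and within-person associations is secondary and conditional: it arises only if time-varying predictors are entered undivided. Under the assumed values in the table its size runs from 0.033 to 0.213 where the true within-person effect is zero. Other ICCs or slopes would give other figures.

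**What to change.** Replace the sentence in Research Questions and Aims with: *This design allows the temporal order of associations to be examined; causal interpretation depends on assumptions about confounding, reverse causation and dropout.* Word the expectations in the Introduction (intervention strategies) and in the Study Overview (impact of past factors) to match.

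Where metabolic, immunological or cognitive predictors that vary over time are entered in GEE or MER, enter the person mean and the deviation from it as separate terms, and rest statements about change on the deviation term.

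The rewording costs almost nothing. The split costs precision, since within-person intervals are wider. For MRI measures, which start at the second wave, the person mean rests on at most three waves. The split also does not make the within-person term causal: if earlier cognition feeds back on the predictor, deviations from a mean that includes later waves are themselves affected. Lagged predictors, marginal structural models or g-computation are options where a causal claim is wanted. They are debatable modelling choices with few waves and are not required by this point.
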